## Abstract

**Background:**

Black smokers have greater difficulty in quitting and higher rates of smoking-related diseases and disabilities than the general population. The smoking disparities experienced by this group are, in part, a consequence of multiple chronic life stressors (eg, racial discrimination) that engender increased exposure to interoceptive stress symptoms (eg, anxiety), which can ultimately lead to smoking as a means of immediate emotion regulation.

**Objective:**

This study aimed to culturally adapt and initially test a novel mobile intervention (ie, Mobile Anxiety Sensitivity Program for Smoking [MASP]) that targets anxiety sensitivity (AS; a proxy for difficulty and responsivity to interoceptive stress) among Black smokers. The MASP intervention is culturally informed to address interoceptive stress management difficulties among Black smokers and is thus hypothesized to facilitate smoking cessation.

**Methods:**

In phase 1, a total of 25 Black smokers with elevated AS will be administered MASP for 6 weeks. Following the completion of phase 1, we will further refine the MASP based on qualitative and quantitative data from participants to produce the final MASP iteration. In phase 2, a total of 200 Black smokers with elevated AS will be enrolled and randomly assigned to receive nicotine replacement therapy and either the smartphone-based National Cancer Institute QuitGuide app for standard mobile smoking cessation treatment or the MASP intervention. All participants in phases 1 and 2 will be enrolled remotely and will complete a web-based study screener; smartphone-based baseline assessment; daily smartphone-based ecological momentary assessments for 6 weeks; phone-based end-of-treatment qualitative interviews; and smartphone-based follow-up assessments at postbaseline weeks 1, 2 (quit date), 3, 4, 5, 6, 28, and 54 (weeks 28 and 54 follow-ups will be completed by phase 2 participants only). The MASP intervention is intended to offset barriers to treatment and encourage treatment engagement via smartphones.

**Results:**

This project was funded in September 2020. Phase 1 data collection began in January 2022. Phase 2 data collection is scheduled to begin in July 2022.

**Conclusions:**

If successful, data from this study will support culturally informed treatment approaches for Black smokers and, pending findings of efficacy, provide an evidence-based mobile intervention for smoking cessation that is ready for dissemination and implementation.

**Trial Registration:**

ClinicalTrials.gov NCT04838236; https://clinicaltrials.gov/ct2/show/NCT04838236

**International Registered Report Identifier (IRRID):**

DERR1-10.2196/38905

## Introduction

Black African American individuals are a tobacco-related health disparity group [1]. The prevalence of smoking among Black adults is 14.4% [2], exceeding that of non-Hispanic White individuals [2], regardless of socioeconomic status [3]. Although Black smokers smoke fewer cigarettes per day [4] and tend to begin smoking later in life than non-Hispanic White individuals [5], they evince greater levels of nicotine dependence [6] and serum cotinine [6-8] and are less likely to maintain abstinence despite more quit attempts [9]. Less quitting success may potentiate mortality rates for cardiovascular disease and other illnesses, which are overrepresented among this group [10]. A major contributing factor to smoking among Black adults appears to be their increased exposure to interoceptive stress symptoms, potentially stemming from and exacerbated by chronic stress related to systemic racism and racial discrimination [4,11-16].

Black adults are a health disparity group for interoceptive problems, including somatic symptoms, anxiety, stress, and pain [13-18], and evince stronger relations between negative emotional states and somatic experiences than White adults [19]. This is notable as Black adults diagnosed with anxiety disorders experience higher rates of hypertension, a condition for which Black adults are almost twice as likely to be diagnosed than White adults [20]. Black adults’ increased awareness of the negative outcomes of physical illnesses may further amplify somatic anxiety and interoceptive distress [21,22]. Anxiety sensitivity (AS) is among the most prominent cross-cultural constructs related to interoceptive distress. AS is a malleable, cognitive-affective factor that reflects the tendency to respond to interoceptive distress and anxiety [23,24]. AS is related to but distinct from negative affectivity and trait anxiety [24-30] and has demonstrated racial and ethnic, gender, age, and time invariance [27,29,31-33].

Smokers with elevated AS report greater tendencies to smoke to reduce negative affect, hold stronger beliefs that smoking will reduce negative affect, smoke in an inflexible manner in response to negative mood, perceive greater barriers to cessation, and experience increased expectations for adverse emotional distress during smoking deprivation [34-37]. The effects of AS on smoking seem to be independent of negative affect states such as anxiety or depression symptoms [38-40]. Smokers with high AS experience more intense nicotine withdrawal and craving during quitting, and higher levels of AS are related to greater odds of early lapse and relapse across clinical and nonclinical samples [41-43]. Withdrawal symptoms might be particularly salient in Black smokers with higher AS, as they may be more apt to perceive these internal sensations as uncontrollable because resources to regulate withdrawal symptoms (ie, adaptive-cognitive and behavioral skills) are likely diminished because of chronic stress exposure (eg, microaggressions, racism, and stress-related burden because of racial discrimination) [44,45]. In turn, Black adults with higher AS may be motivated to smoke to reduce emotional and interoceptive distress.

AS reduction has been integrated into in-person substance use treatment programs among largely non-Black samples [46]. Such programs, originally developed by our team [47,48] and now replicated by other researchers [49-52], have found that reducing AS via cognitive behavioral therapies before quitting increases the odds of smoking cessation [53,54]. Although such effects tend to be the most robust among smokers with higher AS [55], reduction of AS, even among smokers with moderate levels of AS, is helpful in reducing tobacco-related stressors such as withdrawal [55] and improving mental health [56]. However, all previous AS reduction work for smoking has thus far been conducted via in-person approaches within non-Black samples, except for our successful small-scale pilot study, which included a large proportion of Black smokers (66.7%) [57]. Given that smoking can produce perceived or objective acute anxiolytic effects [58], Black smokers with high AS may be more likely to return to smoking following a quit attempt, in part, to alleviate abstinence-induced increases in anxiety, underscoring the need for a culturally tailored intervention to address internal agitation in the context of smoking cessation treatment.

To date, no smoking cessation treatments for Black smokers have focused on sensitivity to interoceptive stress despite the importance of somatic symptoms, including anxiety, stress, and pain, among this population. Furthermore, previous efforts to evaluate the effectiveness of culturally targeted smoking cessation programs for Black smokers have mainly used minimal intervention strategies and group counseling and were nonrandomized trials [59]. We developed and preliminarily tested our novel, integrated, smartphone-delivered intervention for interoceptive stress and smoking (ie, Mobile Anxiety Sensitivity Program for Smoking [MASP]) using a single-arm pilot trial design [57]. This intervention is based on theory and empirical evidence of the importance of interoceptive stress for smokers [60]. The purpose of our initial pilot of the MASP 1.0 (N=12; mean age 45 years; 66.7% Black) was to assess app engagement and determine whether there was an initial signal of app impact on cessation. Participants self-initiated interoceptive exposure exercises 6 times on average, self-initiated *relaxation exercises* 6 times on average, and accessed *treatment audio files* 2 times on average [57]. Biochemically verified abstinence was observed in 25% of the participants at the 6-week follow-up visit (4 weeks after quitting), which are striking and clinically important, given that (1) this was only the initial version of the treatment (MASP 1.0), and (2) smoking cessation success rates for Black smokers are typically low.

The objectives of this National Institute on Minority Health and Health Disparities–funded trial (U54MD015946) are to refine and evaluate the feasibility, acceptability, and efficacy of a novel, culturally tailored, smartphone-delivered MASP app for Black smokers. In phase 1, MASP 1.0 was refined and culturally adapted based on theoretical and empirical guidelines [61] and the initial participant feedback collected during the MASP 1.0 pilot to produce the MASP 2.0. Black smokers with elevated AS (N=25) will use the MASP 2.0 for 6 weeks (ie, the intervention period). Following the intervention period, participants will complete a qualitative interview, which, along with quantitative data and feedback from the community research advisory board as part of the Community Engagement Core of the health institute, will be analyzed to guide intervention refinement to produce MASP 3.0. In phase 2, we will conduct a randomized controlled trial (RCT) of 200 Black smokers with elevated AS who will be randomly assigned to either the MASP 3.0 or the smartphone-based National Cancer Institute (NCI) QuitGuide app, which is considered the smartphone-based standard of care for smoking cessation [62,63]. Mechanisms underlying the intervention effects, including the primary mechanism of AS and secondary mechanisms (ie, anxiety and depression symptoms, stress-based burden of racial or ethnic discrimination, and nicotine withdrawal or craving), will be evaluated. The indirect effects of the MASP intervention (vs QuitGuide) on smoking cessation via these mechanisms of change will be evaluated. Finally, we will explore whether stress associated with perceived racial discrimination, acculturation, ethnic identity, and COVID-19 may function as moderators of smoking outcomes.

## Methods

### Ethics Approval

The University of Houston (reference number: 12747) and the University of Oklahoma Health Sciences Center (reference number: STUDY00000360) institutional review boards approved the protocol presented in this study. This trial was registered at ClinicalTrials.gov (NCT04838236).

### Study Eligibility

Adults aged ≥18 years are eligible to participate in this study if they self-identify as Black and report high AS (ie, Short Scale Anxiety Sensitivity Index [64] score of ≥5), daily smoking (minimum of 10 cigarettes per day) for at least 2 years, motivation to quit smoking (>5 on a 10-point scale) [65], willingness to complete all study surveys and assessments, willingness to use nicotine replacement medications (nicotine replacement therapy [NRT]; nicotine patch and lozenges), and desire to quit smoking 2 weeks after completion of the baseline survey and receipt of study materials. The exclusion criteria include current or intended participation in a concurrent substance use treatment program, ongoing psychotherapy of any duration directed specifically toward the treatment of anxiety or depression, not being fluent in English, current use of any pharmacotherapy or psychotherapy for smoking cessation not provided by this study, a legal status that would interfere with participation, cognitive impairment (assessed via the 6-item Cognitive Impairment Test [66]), being non-Black, and being aged <18 years. Those who participated in the previous phase of the study are not eligible to participate in future study stages.

### Recruitment and Procedure

Participant enrollment in the study and all study procedures will be conducted remotely. We will advertise through community organizations that promote smoking cessation initiatives, social media, and internet outlets. Study screening will be completed via REDCap (Research Electronic Data Capture; Vanderbilt University) when a participant clicks on the study advertisement. Individuals who prescreen as eligible via the REDCap assessment will be phoned to provide informed consent and complete the final eligibility screening for the study. To reduce the likelihood of fraudulent enrollments in the study, potential participants will be required to text a picture of their pack of cigarettes in real time as evidence that they are smokers, and they will be required to text a picture of their ID or a piece of mail with their name and address on it. Persons who will be deemed eligible and willing to participate during the enrollment phone call will be provided with information about the purpose, goals, and procedures of the study and asked to download the Insight app (University of Oklahoma Health Sciences Center) onto their personal smartphone or mailed a smartphone if they do not have one that is compatible with the Insight platform.

Once the Insight app is downloaded, participants will be given a unique single-use code that will enable them to use the app to complete the baseline assessment on their personal or study-provided smartphone. After the baseline assessment is completed, participants will be mailed a Bedfont iCOquit smokerlyzer, which reports levels of carbon monoxide (CO) in expired breath to verify self-reported smoking status (phases 1 and 2). Upon receipt of the iCO, participants will complete a brief phone call with the study staff to review all app functions and be oriented to the iCO. In phase 2, REDCap will be used to randomize participants to the MASP 3.0 or QuitGuide during this brief call. Participants will then use the assigned intervention via the app for 6 weeks and complete daily ecological momentary assessments (EMAs) during the intervention period. App-based follow-ups will occur 1, 2, 3, 4, 5, and 6 weeks after the baseline for all participants; phase 2 participants will also complete follow-ups at 28 and 54 weeks after the baseline. All interactions with the QuitGuide and MASP apps will be date- and time-stamped, and the app feature use will be recorded for future analysis. All daily surveys and follow-up assessments (both treatment arms) will be completed using the Insight app, and a phone-based qualitative interview will be completed at the end of the 6-week intervention period. We have developed a system of procedures that includes contacting participants to encourage retention (ie, calling, texting, and emailing participants who have not completed follow-up assessments). Participants who will borrow smartphones will be asked to return them after the final follow-up assessment. In addition to randomization in phase 2, similar procedures will be followed in phases 1 and 2 (Figure 1).

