#### NCI QuitGuide Condition

The NCI QuitGuide app is a free smartphone app available through Smokefree.gov. QuitGuide is one of the few apps that are consistent with many of the recommendations of the Clinical Practice Guidelines for quitting smoking [68]. Individual-level app feature use is accessible by request from Smokefree.gov server. The QuitGuide app aims to help smokers understand their smoking patterns and develop the skills needed to quit smoking. Participants who are randomly assigned to the QuitGuide condition will use their personal smartphone or receive a study smartphone if they do not have one, which will be preloaded with the QuitGuide app and preset for a quit date 2 weeks after randomization into an intervention group. Participants will receive information on how to use the QuitGuide app features during the randomization phone call. QuitGuide participants will also download an Insight EMA app stripped of all the MASP intervention features. Table 1 for a list of QuitGuide features.

**Table 1 table1:** Comparison of phase 2 treatment conditions.

App components			MASP^a^		QuitGuide
EMA^b^			✓		✓ (add-on for this study)
Set a quit date			Quit date set to 2 weeks after randomization and receipt of the iCO via mail		Quit date set to 2 weeks after randomization and receipt of the iCO via mail
Share quit information on social media					✓
Smoking cessation psychoeducation			✓		✓
Content specific to Black smokers			✓		
NRT^c^ tips and use advice			✓		
AS^d^ psychoeducation			✓		

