#### Follow-up Assessments

Follow-up assessments will be completed using the Insight app at weeks 1, 2 (quit date), 3, 4, 5, 6, 28, and 54 (52 weeks after quitting). Follow-up surveys will be distinguishable from EMAs (ie, participants will self-initiate the assessment by clicking a button labeled *Follow-up Survey* and receive separate compensation for completing these assessments). Importantly, participants will also be asked to complete a phone-based qualitative interview with the study staff at the 6-week follow-up (phase 1 and phase 2). If a participant does not complete the brief app-based follow-up assessments, they will be contacted via call, text, and email to remind them to complete them.

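### Follow-ups are dated from baseline but the quit date from a later call, so the week labels agree only if mailing the iCO takes no time

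*Protocol article*

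**What the plan says.** The protocol article describes this order of events under Recruitment and Procedure. The participant completes the baseline assessment in the Insight app. Then: "After the baseline assessment is completed, participants will be mailed a Bedfont iCOquit smokerlyzer". When it arrives, staff hold an orientation call, and in phase 2 "REDCap will be used to randomize participants to the MASP 3.0 or QuitGuide during this brief call". The six-week intervention starts after that call.

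The quit date follows the call. Table 1, which compares the phase 2 conditions, gives for both arms: "Quit date set to 2 weeks after randomization and receipt of the iCO via mail". The QuitGuide text agrees: "preset for a quit date 2 weeks after randomization into an intervention group". Phase 1 has no randomization. The nearest wording that covers it is the criterion in Study Eligibility: "desire to quit smoking 2 weeks after completion of the baseline survey and receipt of study materials".

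The follow-ups are counted from elsewhere. Recruitment and Procedure says "App-based follow-ups will occur 1, 2, 3, 4, 5, and 6 weeks after the baseline for all participants" and "phase 2 participants will also complete follow-ups at 28 and 54 weeks after the baseline". The Abstract and the Compensation section also count from baseline. Follow-up Assessments then lists "weeks 1, 2 (quit date), 3, 4, 5, 6, 28, and 54 (52 weeks after quitting", which treats week 2 as the quit date.

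Smoking Outcomes uses the quit date as its origin. It sets the primary 7-day point prevalence abstinence (PPA) at 4 weeks (phase 1) or 52 weeks (phase 2) from the scheduled quit date, and CO checks on the quit date and 1 to 4, 26 and 52 weeks later.

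**The concern.** A device mailed after baseline and received before the call makes the gap between baseline and the call longer than zero. The baseline clock and the quit-date clock then differ by that gap, yet the article uses one set of week numbers for both.

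Two people could build different schedules from this text, and each could point to a sentence in support. If the baseline clock is used, three things suffer:

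- **Early PPA.** Statistical Analyses requires no smoking in the seven days before an assessment and compares arms at each follow-up. Days before the quit date would enter the early windows. Someone who smokes up to the quit date and stops exactly on schedule would be scored as not abstinent.
- **The phase 1 primary outcome.** The week-6 visit would come earlier than four weeks after quitting.
- **The time axis of the latent growth models.** The delay differs between participants, so one nominal week would represent different times since quitting.

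**Working it through.** **Inputs.** Follow-ups at weeks w = 1, 2, 3, 4, 5, 6, 28 and 54 from baseline (Recruitment and Procedure). Quit date 14 days after the call (Table 1). Look-back of 7 days (Statistical Analyses). Delay d, in days from the baseline survey to the call: not given, so 3 to 14 days is assumed. For phase 1, d is the time to receipt of materials, on the reading that the two weeks in Study Eligibility start once both conditions are met.

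**Formulas.**

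- Quit date = baseline + d + 14.
- Days since quit date at week w: t = 7w − 14 − d.
- Pre-quit days in the look-back: the smaller of 7 and (7 − t), and never below 0. At week 3, t = 7 − d, so this is min(d, 7).

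**The article's own labels.** With d = 0, week 2 gives t = 0. Week 6 gives 42 − 14 = 28 days (4 weeks), week 28 gives 196 − 14 = 182 days (26 weeks), and week 54 gives 378 − 14 = 364 days (52 weeks). Every label is reproduced, but only at d = 0.

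**With a delay, and visits dated from baseline** (days since the scheduled quit date; pre-quit days in the window in brackets for weeks 3 and 4):

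| d | Week 2 | Week 3 | Week 4 | Week 6 | Week 54 |
|---|---|---|---|---|---|
| 0 | 0 | 7 (0) | 14 (0) | 28 | 364 |
| 3 | −3 | 4 (3) | 11 (0) | 25 | 361 |
| 7 | −7 | 0 (7) | 7 (0) | 21 | 357 |
| 10 | −10 | −3 (7) | 4 (3) | 18 | 354 |
| 14 | −14 | −7 (7) | 0 (7) | 14 | 350 |

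**Relative size of the shift.**

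- At 4 weeks: d/28 = 10.7% (d = 3), 25% (d = 7), 50% (d = 14).
- At 52 weeks: d/364 = 0.8%, 1.9%, 3.8%.

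**Limits within this range.** At week 6, t is at least 14, so the look-back lies wholly after the quit date. The phase 1 primary outcome would be mistimed, but its window would contain no pre-quit days.

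**With visits dated from the call or the quit date.** Weeks 2, 3, 4, 5, 6, 28 and 54 fall 0, 1, 2, 3, 4, 26 and 52 weeks after the quit date for any d.

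**The case against.** The strongest reply is that baseline is loose wording for study start, and that a single clock starting at the call fits nearly everything else. The intervention begins after the call and has two pre-quit and four post-quit weeks. The interview is placed both at the end of the intervention and at the 6-week follow-up, which is one date only on the call clock. Read literally, the baseline clock puts the week-1 visit on the day of randomization at d = 7, and a week before it at d = 14. Smoking Outcomes already counts the primary outcome from the quit date. The participant-flow figure and the full protocol are not shown and might name the origin.

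Much of this stands. A call-based clock may well be what is intended, and the documents do not show that any assessment is in fact mistimed. But the text does not say so. The Baseline Assessment section defines baseline as the app survey, and the randomization paragraph places randomization after it. The conflict is between statements the article makes, not a detail left to another document.

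A reader might infer more: that every post-quit outcome is shifted and that the phase 2 primary comparison is compromised. The documents do not support that, for three reasons:

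- The delay precedes randomization, so it should be similar in both arms and would not by itself bias the comparison.
- Time to lapse can be taken from daily self-report and date-stamped EMA and lapse reports, without using visit dates.
- The Table 1 quit-date rule applies to phase 2 only, so the phase 1 argument rests on the less explicit eligibility wording.

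**Conclusion.** The contradiction is real: the stated sequence, the baseline-dated follow-ups and the week labels agree only with a zero mailing delay. Harm is conditional on visits being scheduled from baseline as Recruitment and Procedure states, and its size rests on the assumed 3 to 14 days. On those terms, the week-3 PPA is seriously affected, week 4 is affected once d exceeds 7, and the phase 1 primary outcome is measured 3 to 14 days early. The growth-model time axis is blurred by variation in d. The phase 2 primary outcome moves little, and the validity of its between-arm comparison is not in question. Severity: moderate.

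**What to change.** State one time zero for all follow-ups, EMA bursts and PPA windows: either the iCO orientation call (the randomization call in phase 2) or the scheduled quit date derived from it. Keep the baseline survey as a pre-randomization measure only. Then reconcile these places:

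- Abstract, Recruitment and Procedure, and Compensation: replace the counts from baseline.
- Study Eligibility and Table 1: express the quit date on the same clock, and state explicitly how it is set in phase 1.
- Follow-up Assessments and Smoking Outcomes: confirm that both week numberings follow from that origin.
- Compensation: EMA weeks are given as 1 to 6, 28 and 54, but payment follows weeks 6, 26 and 54. Use one numbering.

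For phase 1 assessments already collected, report the actual days since the scheduled quit date.

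The cost is a scheduling setting in the app or database and wording changes. Sample size and the outcome definition are untouched. It should be settled before phase 2 enrolment starts.
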